## Abstract

**Background:**

Behçet’s syndrome (BS) is a systemic inflammatory disorder of unknown etiology, and it is characterized by a wide range of potential clinical manifestations. Recent evidence suggests that the gut microbiota (GM) in BS has low biodiversity with a significant depletion in butyrate producers. The aim of the present project is to investigate whether a dietary intervention could ameliorate the clinical manifestations and modulate the GM of individuals with BS.

**Methods:**

This is a randomized, open, cross-over study that involves 90 individuals with BS, who will be randomly assigned to one of three different diets for 3 months: a lacto-ovo-vegetarian diet (VD), a Mediterranean diet (MD), or a Mediterranean diet supplemented with butyrate (MD-Bt). The VD will contain inulin-resistant and resistant-starch-rich foods, eggs, and dairy in addition to plant-based food, but it will not contain meat, poultry, or fish. The MD will contain all food categories and will provide two portions per week of fish and three portions per week of fresh and processed meat. The MD-Bt will be similar to the MD but supplemented with 1.8 g/day of oral butyrate. The three different diets will be isocaloric and related to the participants’ nutritional requirements. Anthropometric measurements, body composition, blood, and fecal samples will be obtained from each participant at the beginning and the end of each intervention phase. The primary outcomes will be represented by the change from baseline of the BS gastrointestinal and systemic symptoms. Changes from baseline in GM composition, short-chain fatty acid (SCFA) production, and the inflammatory and antioxidant profile will be considered as secondary outcomes.

**Discussion:**

BS is a rare disease, and, actually, not all the available treatments are target therapies. A supportive treatment based on dietary and lifestyle issues, able to restore immune system homeostasis, could have a high impact on cost sustainability for the treatment of such a chronic and disabling inflammatory condition.

**Trial registration:**

clinicaltrials.gov: NCT03962335. Registered on 21 May 2019.

## Introduction

Behçet’s syndrome (BS) is a systemic inflammatory disorder characterized by a wide range of potential clinical manifestations with no gold-standard therapy [1, 2]. Although the pathogenesis of BS is currently unknown, it has been recently classified as a type of systemic vasculitis [3]. The gut microbiota (GM) is recognized to deeply influence our metabolic and immunological health, and specific dysbiotic GM configurations indicate a fascinating link between intestinal microbes and health status. A recent study from our group [4] showed, for the first time, that a peculiar dysbiosis of the GM is present also in individuals with BS, in line with several other chronic disorders [5–7]. Moreover, individuals with BS have significant depletion of well-known butyrate producers, i.e. *Roseburia* and *Subdoligranulum*, and a consistent decrease in butyrate, one of the most representative short-chain fatty acids (SCFAs), thus suggesting an increase in the inflammatory state [8, 9].

In this context, over recent years, growing evidence has suggested that high-fiber dietary patterns promote a more favorable GM profile, and are key mediators of microbial diversity [10, 11]. Lacto-ovo-vegetarian diet is characterized by abstention from consuming meat and meat products, poultry, seafood, and flesh from any other animal and by consuming a large amount of plant-derived foods. This dietary pattern has been largely demonstrated to be beneficial both in patients with established disease and in people with with traditional risk factors for chronic diseases [12, 13]. In particular, it has recently been demonstrated that high adherence to a lacto-ovo-vegetarian diet is associated with a beneficial GM profile, with enrichment in fiber-degrading bacteria and an increase in fecal SCFAs [14]. Similarly, other dietary patterns rich in plant-based food, such as the Mediterranean diet, have been shown to modulate GM dysbiosis, by supporting the recovery of a balanced microbial community of health-promoting SCFA-producing members with the decrease in pro-inflammatory pathobiont groups [15, 16]. Furthermore, current evidence indicates that the consumption of certain fibers - such as inulin and resistant starch - leads to specific GM rearrangements with consequent butyrate hyperproduction in humans [17]. All these findings let us hypothesize that the adherence to a controlled dietary profile enriched in substrates with potential for butyrate production may select for butyrate-producing bacteria - such as *Roseburia* spp. and *Faecalibacterium prausnitzii* - so reversing the pro-inflammatory dysbiosis observed in BS.

Thus, the aim of the present project is to conduct an open, randomized, cross-over dietary intervention trial to investigate whether a lacto-ovo-vegetarian diet enriched in substrates with potential for butyrate production or a Mediterranean diet supplemented with butyrate could be beneficial for the GM and the amelioration of the clinical manifestations and disease severity in individuals with BS.

## Methods: participants, interventions, and outcomes

### Study design

The randomized, open, cross-over clinical trial will be conducted at the Careggi University Hospital, Florence, Italy. A cross-over design will be implemented to allow comparison of a lacto-ovo-vegetarian diet (VD), a Mediterranean diet supplemented with butyrate (MD-Bt), and a Mediterranean diet without any supplement (MD), as control, within the same individual. Participants will act as their own controls in cross-over studies, so individual differences will be controlled for, making the error variance smaller and subsequently reducing the sample size required to find a significant effect due to increased statistical power. The study design follows the Standard protocol items: recommendation for interventional trials (SPIRIT) guidelines (see Fig. 1 and supplementary file #1).

**Fig. 1 Fig1:**
[figure not shown]
Schedule of enrollment, interventions, and assessments for participants. SSS, Symptom Severity Scale; GAI, Global Assessment of Improvement Scale; BDCA, Behçet Disease Current Activity Form; mo, month

### Eligibility criteria

Inclusion criteria include diagnosis of BS, age 18–65 years, willing to give informed consent, and willing to participate in a study where one of the proposed diets has a vegetarian pattern.

Exclusion criteria include pregnancy or lactation; concomitant presence of serious illness or unstable condition (other immune-mediated or autoimmune diseases, including inflammatory bowel diseases); chronic viral infections; malignancies; recent myocardial infarction; chronic liver disease; current or recent (past 6 months) participation in a weight loss treatment program or use of weight loss medication; adoption of a vegetarian diet for the past 3 months; antibiotic, prebiotic, or probiotic use in the past 3 months; and current or previous (past 6 months) infection with SARS-CoV-2.

### Interventions and participant timeline

This clinical randomized study has a cross-over design with three intervention periods and two wash-out periods. After a 2-week run-in period - which will be used to assess participants’ eligibility and to collect demographic details, signed informed consent, and 3-day dietary records - the eligible participants (*N* = 90) will be randomly assigned to follow a 3-month dietary profile with a VD, a MD or a MD-Bt. The VD will contain inulin and resistant-starch-rich foods, eggs, and dairy, in addition to plant-based food, but will not contain meat, poultry, or fish. The MD will contain all the food categories and will provide two portions per week of fish and three portions per week of fresh and processed meat (one of which will consist of fresh or processed red meat). The MD-Bt will be similar to the MD but supplemented with 1.8 g/day of oral butyrate. The three different dietary patterns will be isocaloric and related to the participants’ nutritional requirements, with about 50–55% of energy derived from carbohydrates, < 30% from fats, and 15–20% from proteins. Participants will prepare their meals or eat at restaurants. Alcoholic beverages will be limited to two per day for men and one per day for women. Interventions will be delivered by a dietitian through face-to-face, individual counseling sessions at the Careggi University Hospital. Participants will be provided with a detailed, 1-week menu plan with portions expressed in grams or milliliters as appropriate, and tips and information on the food groups that can be included and those that cannot. The VD plan will also include recipes for preparing meals.

The study design is depicted in Fig. 2. There will be six clinical evaluations of the study population: at baseline before starting the nutritional interventions (T0), 3 months after the onset of the first nutritional intervention (T1), at the end of the first wash-out period, lasting 1.5 months, when individuals will be allowed to resume their normal eating habits, at the onset of the second intervention (T2) at 7.5 months after the onset of the study, at the end of the second nutritional intervention (T3), at the beginning of the third nutritional intervention and at the end of the wash-out period, lasting again 1.5 months (T4), and at the end of the third nutritional intervention (T5).

**Fig. 2 Fig2:**
[figure not shown]
Study design. VD, vegetarian diet; MD, Mediterranean diet; MD-Bt, Mediterranean diet supplemented with butyrate

During the baseline visit, participants will be instructed on the objectives and methods of the clinical trial and will be asked not to alter their physical exercise habits during the study. Anthropometric measurements, body composition, and blood, urine, and stool samples will be obtained from each participant at the beginning and the end of each intervention phase. The clinical manifestations and disease severity of BS, especially symptoms involving the gastrointestinal system, will be assessed using a modified version of two questionnaires originally computed for individuals with inflammatory bowel disease: the Global Assessment of Improvement Scale (GAI) and the Symptom Severity Scale (SSS). Disease activity will be assessed by the validated Behçet Disease Current Activity Form (BDCAF), which consists of objective and subjective items, and considers the symptoms present over the 4 weeks before the assessment. Each participant will have to complete a 3-day dietary record (two weekdays and a weekend day) before starting and a dietician will analyze all 3-day dietary records using a country-specific food-nutrient database.

### Outcome measures

#### Primary outcomes

Primary outcomes will be assessed through validated questionnaires, to analyze the progression of BS. The metric used will be changes in means from the beginning to the end of each dietary intervention. They will include:
Severity of gastrointestinal symptoms assessed by the SSS modified form. The SSS is a multidimensional rating scale assessing overall symptom severity on a visual analogue scale (VAS). An overall score will be calculated from six items: pain severity, pain frequency, abdominal bloating, dissatisfactory bowel habit, abdominal heaviness, and life interference. The modified SSS ranges from 0 to 600, with higher scores meaning more severe symptoms.Improvement of gastrointestinal-related BS symptoms assessed by the GAI modified form. The GAI will assess improvement of symptoms of BS using a 7-point scale, with higher scores meaning an improvement in the symptoms. The severity of abdominal pain, severity of abdominal distention, satisfaction with bowel habits, severity of headache, severity of exhaustion, severity of nausea, attention disorder, muscle/joint pain, and quality of life will be investigated in response to the following question: “Compared to the way you felt before you entered the study, have your symptoms over the past 7 days been: 1) “Substantially Worse”, 2)” Moderately Worse, 3)” Slightly Worse”, 4)” No Change”, 5)” Slightly Improved”, 6)” Moderately Improved” or 7) “Substantially Improved”.Disease severity in BS assessed by the BDCAF. The BDCAF will assess the presence of oral and genital ulceration, skin, joint, and gastrointestinal involvement, presence of fatigue and headache, using a 5-point scale according to the duration of symptoms, with 0 meaning no symptoms and 4 meaning symptoms for 4 weeks. The presence of eye, large vessel, or central nervous system (CNS) involvement will be documented with “yes/no” answers. In addition, individuals will be asked to rate on a 7-point scale how active they felt. Similarly, clinicians will complete a 7-point rating scale to assess their opinion of overall disease activity, with lower scores representing better outcomes.

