### Sample size calculation

Due to the lack of dietary intervention trials on BS and to the fact that gastrointestinal symptoms are quite similar in BS and inflammatory bowel disease, based on a previously published trial [24], a sample size of 80 individuals with BS is required to achieve power of 80% (beta) with alpha = 0.05, to detect a 50-point difference in the mean of SSS (the primary outcome), between VD and MD interventions. We will recruit an extra 10 volunteers (for a total of 90), as we assume that not all individuals would be compliant with the treatments and in case of loss to follow up. Losses will be included in the intention-to-treat but not in the per-protocol analyses.

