### Statistical analysis

The results will be expressed as mean plus/minus SD, median and range, or geometric mean with 95% confidence intervals (CIs) as appropriate. Categorical variables will be presented as frequencies and percentages. All data will be treated as paired samples from a cross-over study. The three interventions will be analyzed combining the results obtained in the three phases of the three groups. Outcomes will be analyzed within each group using the paired comparison Student’s *t* test to test whether the changes are statistically significant. The absolute change (mean baseline value subtracted from mean value after each intervention) will be estimated using the independent samples *t* test.

Raw sequences will be processed in the GM analysis, using a pipeline that combines PANDAseq [25] and QIIME [26]. The UCLUST software [27] will be used to bin high-quality reads into operational taxonomic units (OTUs) at 0.97 similarity threshold through an open-reference strategy. Taxonomy will be assigned through the Ribosomal Database Project (RDP) classifier, using the Greengenes database as a reference. Alpha diversity and rarefaction curves will be computed using different metrics, including the Faith’s phylogenetic diversity, the number of observed OTUs and the Shannon index. Beta diversity will be estimated by weighted and unweighted UniFrac distances, which will be used as input for principal coordinates analysis (PCoA). All statistical analysis will be performed using R and the packages vegan, stats, and made4. The significance of data separation in the PCoA will be tested using a permutation test with pseudo-F ratios (function Adonis in vegan). The Wilcoxon test for paired data will be used to assess significant differences in alpha diversity and taxon relative abundance between groups, and the Kruskal–Wallis test will be used for multiple comparisons. The *p* values will be corrected for false discovery rate (FDR) using the Benjamini-Hochberg method.

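### Subtracting each period's baseline, with no baseline covariate, probably gives away precision that a within-person covariate model would keep if carry-over is negligible

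*Protocol article*

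**What the plan says.** Under Primary outcomes the article fixes the metric: "The metric used will be changes in means from the beginning to the end of each dietary intervention". Secondary outcomes repeats it for the blood, urine and stool measures. Each of the three diet periods has its own starting visit (T0, T2, T4) and closing visit (T1, T3, T5).

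The Statistical analysis section declares: "All data will be treated as paired samples from a cross-over study". It then describes two tests.
- A paired t test within a diet: "Outcomes will be analyzed within each group using the paired comparison Student".
- An unpaired t test for the size of the change: "The absolute change (mean baseline value subtracted from mean value after each intervention) will be estimated using the independent samples".

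No baseline covariate is named for the clinical outcomes. Adjustment for treatment order appears only in the microbiota PERMANOVA.

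Study design justifies the cross-over by smaller error variance, "reducing the sample size required to find a significant effect due to increased statistical power". Sample size calculation states "a sample size of 80 individuals with BS is required to achieve power of 80% (beta) with alpha = 0.05". The target there is a VD against MD contrast of 50 SSS points. The section cites a published trial and prints no SD or correlation.

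**The concern.** In a cross-over, stable differences between people already cancel when one person's end-of-diet scores are compared. The period baselines can still help, but how much weight they deserve depends on how strongly a person's baseline differences predict the end-score differences. A change score sets that weight at 1 whatever the data show. For a self-rated symptom score measured three months apart, the best weight is probably below 1, and the excess weight adds noise to the diet comparison.

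At stake is part of the power that the design was chosen to deliver, in a rare disease with a target of 80 participants plus 10 for losses. The baselines needed to do better are already collected.

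**Working it through.** **Inputs from the protocol article.** N = 80, power 80%, alpha 0.05 (two-sided assumed), 50 SSS points between VD and MD. Visits are taken at months 0, 3, 4.5, 7.5, 9 and 12, from 3-month diets and 1.5-month wash-outs. Interventions and participant timeline puts T2 at 7.5 months, but 3 + 1.5 = 4.5; I used 4.5, and the text needs reconciling.

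**The plan's own figure.** N = 80 cannot be reproduced without an SD. Solving backwards with 1.96 + 0.84 = 2.80:
- 80 pairs: SD of the paired difference = 50 × √80 / 2.80 = 159.6
- 80 against 80 as independent samples: SD = 50 × √40 / 2.80 = 112.9
- two groups of 40: SD = 50 × √20 / 2.80 = 79.8

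The text does not say which was meant.

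**Variances.** For two diets in one person, let dY be the difference in end scores, dX the difference in period baselines, and b = Cov(dX, dY) / Var(dX).
- End score only: Var(dY)
- Change: Var(dY) + Var(dX) − 2 Cov
- Baseline as within-person covariate: Var(dY) − Cov² / Var(dX)

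Change minus covariate equals Var(dX)(1 − b)². This is never negative and is zero only at b = 1. With equal variances, covariate/change is R = (1 + b)/2 and change/end score is 2(1 − b). Subtraction therefore does worse than the unadjusted end score only when b < 0.5.

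**Power if a paired change contrast has 80%.** Power = Φ(2.80/√R − 1.96). The correlations are assumptions; unit variance per visit.
- *Equal correlation ρ among visits.* Cov = 0; change 4(1 − ρ), covariate 2(1 − ρ). R = 0.50, power 97.7%.
- *Correlation fading, 0.5 per 3 months.* Averaged over the three period pairs, change 2.277, covariate 1.348. R = 0.59, power 95%.
- *Correlation fading, 0.8 per 3 months.* R = 0.67, power 93%.
- *Person 0.3, period 0.4, error 0.3.* Var(dY) = Var(dX) = 1.40, Cov = 0.80, b = 0.57. Change = 1.40 + 1.40 − 1.60 = 1.20; covariate = 1.40 − 0.64/1.40 = 0.943. R = 0.79, power 88% to 89%. Here the end score alone (1.40) is less precise than change (1.20).

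By slope, with equal variances:

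| b | R | N for 80% power (80 × R) | Power at N = 80 |
|---|---|---|---|
| 0 | 0.50 | 40 | 97.7% |
| 0.5 | 0.75 | 60 | 89.9% |
| 0.7 | 0.85 | 68 | 86.0% |
| 0.9 | 0.95 | 76 | 82.0% |
| 1 | 1.00 | 80 | no gain |

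**Simulation, no carry-over.** Three-period cross-over, 78 participants, SD 100, effect 25, four correlation patterns. Power for change against covariate: 35% v 60%, 56% v 75%, 98% v 99.7%, 37% v 56%.

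**Cost of estimating the slope.** At b = 1, simulated power was 79.4% with the covariate and 79.8% for change at n = 80, and 74% against 79% at n = 12.

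**Carry-over.** True effect −50, six sequences assumed:
- 30% of the previous effect left in the baseline only: change −55.7, covariate −50.3.
- 50% left in both baseline and end score: change −50.0, covariate −41.9.

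These biases depend on the sequence set, which the text does not list. With three cyclic sequences and only VD active, both analyses stayed close to −50.

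**The case against.** A change score is a legitimate metric, and the article contains no error on this point alone; the issue is efficiency of unknown size. Several further objections stand.

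- A reader might infer that subtracting the baseline always inflates the variance. The documents do not support that. Against the unadjusted end score the direction depends on the slope, and no correlation is given. In the person-plus-period case above, subtraction lowers the variance.
- A reader might infer that covariate adjustment is never worse and costs nothing. It uses one estimated slope, and it is biased when carry-over persists in both baseline and end score, where change is not. With 1.5-month wash-outs, neither carry-over pattern can be excluded.
- The 80% starting point presupposes a paired change contrast. The section names an independent-samples test for the change, which sits badly with its own statement about paired samples. That has to be repaired first, and the covariate is a refinement of the repaired analysis.
- The metric itself may stay. With the same baseline terms in the model, regressing the change or the end score gives the same diet estimate.
- The algebra is for one continuous score. The article defines no BDCAF total, and the GAI asks about change since before study entry, so it has no period baseline to adjust for.

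None of this removes the precision argument for the SSS when carry-over is negligible.

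**Conclusion.** The point holds as a probable loss of precision, not as an error. The article fixes change from each period's own baseline, tested without a baseline covariate, and so imposes a slope of 1. If carry-over is negligible, a within-person covariate analysis is at least as precise in large samples, and clearly more so unless the slope is near 1.

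The size is conditional. From 80% for a paired change contrast, power would rise to between 88% and 98% over the correlation patterns examined, to 82% at slope 0.9, and hardly at all at slope 1. The 98% figure should not be read as the expected gain, because it needs correlation that does not fade over the 12 months. The plan's own N = 80 cannot show where in this range the trial lies.

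**What to change.** In Statistical analysis, replace the independent-samples t test on change with a cross-over mixed model containing participant, period and diet. Add the period baseline, split into the participant's mean baseline and that period's deviation from it. Apply the model to the SSS, the continuous laboratory outcomes and any BDCAF score that is defined and treated as continuous. Leave the GAI out.

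The outcome may be the end score or the change, so the metric under Primary outcomes need not be altered. Report the unadjusted change contrast from the same model as a sensitivity analysis, because carry-over affects the two analyses differently.

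The cost is analysis wording only, since the T0, T2 and T4 values are already planned. Two small downsides should be stated: one estimated slope (about 0.4 percentage points of power at n = 80 if the slope is 1) and reliance on negligible carry-over.
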